### Data analysis

2.7

All statistical analyses will be performed using the SPSS statistical package program, version 17.0 (SPSS Inc., Chicago, IL). Chi-square tests will be applied for categorical data and Analysis of variance tests will be applied for continuous data. Logistic regression will be used to estimate the odds ratio and the probability of a binary response, based on one or more independent variables. *P*-values <.05 will be considered statistically significance.

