### Participants

2.2

Patients will be recruited from the outpatients of the Department of Hepatogastroenterology of Kaohsiung Chang Gung Memorial Hospital (KCGMH) in Kaohsiung, Taiwan.

Patients will be eligible if they satisfy the following criteria: age over 20 years old; with upper gastrointestinal symptoms, or who without symptoms and visit clinic for health examination; meet the criteria for examination via endoscopy; volunteered to join this research and signed the institutional review board agreement. Both men and women will be enrolled.

Patients with any of the following conditions will be excluded: hypertension, diabetes, hepatitis, or other systemic diseases; pregnancy; acute infection; cognitive impairment; unable to protrude the tongue stably; risk of temporomandibular joint dislocation.

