### Study design

2.3

This protocol is a cross-sectional, case-controlled observational study investigating the usefulness of the ATDS in clinical practice by examining its efficacy as a diagnostic tool for upper gastrointestinal disorders.

After giving their consent, participants will undergo tongue image capturing using the ATDS. The ATDS examination will be performed under constant environmental conditions and by the same educated operator. After capturing tongue image, participants accept panendoscopy which will be performed by a professional gastroenterology doctor. According to findings of panendoscopy, the participants will be allocated to the following 4 groups: a peptic ulcer disease group (PUD, including patients diagnosed with peptic ulcers), a gastroesophageal reflux group (GERD, including patients diagnosed with reflux esophagitis or gastroesophageal reflux), a gastritis group (GA, including patients diagnosed with gastritis), and a healthy group (H, including patients with negative results from the gastric endoscopy procedure). A flow chart of the trial design is presented in Fig. 1.

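### Endoscopy-defined, unmatched groups are compared with unadjusted chi-square and ANOVA, so age or sex differences could be mistaken for disease effects on the tongue

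*Protocol article*

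**What the plan says.** All references are to the protocol article.

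- **Design (2.3).** "This protocol is a cross-sectional, case-controlled observational study investigating the usefulness of the ATDS in clinical practice". Group membership follows the examination: "According to findings of panendoscopy, the participants will be allocated to the following 4 groups". The groups are peptic ulcer disease, GERD, gastritis and healthy.
- **Who enters (2.2).** The age criterion is "age over 20 years old", with no upper limit. On sex: "Both men and women will be enrolled". Participants are people "with upper gastrointestinal symptoms, or who without symptoms and visit clinic for health examination", so symptomatic outpatients and health-check attenders are combined.
- **What is restricted (2.2).** Exclusions include "hypertension, diabetes, hepatitis, or other systemic diseases; pregnancy; acute infection". Sex is not restricted, and neither is age above the lower limit.
- **Analysis (2.7).** "Chi-square tests will be applied for categorical data and Analysis of variance tests will be applied for continuous data". Then: "Logistic regression will be used to estimate the odds ratio and the probability of a binary response, based on one or more independent variables". The response and the independent variables are not named.

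Nowhere in the article does age or sex appear as a matching factor, a stratum or a covariate.

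**The concern.** Randomisation would make the groups comparable in age and sex on average. Here a diagnosis forms them, and people who attend for a health check may well differ in age or sex from people who come with symptoms. A chi-square test of feature by group, or an ANOVA with group as its only factor, compares the groups as they are found. If a feature such as fissures or fur thickness varies with age, and the groups differ in age, the test picks up the age difference.

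The nine tongue features are the primary outcomes (2.5.1). The Discussion wants to know how the diseases differ from each other on tongue images, and it expects tongue diagnosis to serve as a preliminary screening index. A feature that merely tracks age or sex would support neither use, because the clinician already knows both. A larger sample does not help: the bias stays the same while the test becomes more sensitive to it.

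**Working it through.** **1. The plan's own number.** Section 2.6 gives 517 from power 0.9, alpha 0.05, an effect size of 0.3 and 10% drop-out. A two-sided two-sample t-test at a standardised difference of 0.3 needs 235 per group, or 470 in total, and 470 × 1.10 = 517. The figure therefore reproduces as an unadjusted two-group comparison with no covariate term. I take about 470 analysed; in four equal groups that is 117 each, N = 468. Equal groups are an assumption.

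**2. Assumed inputs (not in the documents).**
- no disease effect on the feature
- feature-age correlation ρ = 0.2 to 0.3
- healthy group 0.5 age SD apart from the three disease groups, which share one mean age
- within-group SD of the feature set to 1

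**3. Spurious difference.** d = ρ × age gap in SD:
- 0.2 × 0.5 = 0.10 SD
- 0.3 × 0.5 = 0.15 SD

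**4. Four-group ANOVA.** With one mean shifted by d, the variance of the four means is f² = (1/4)(3/4)d² = 0.1875 d². The noncentrality is λ = N f², and the test uses F with 3 and 464 degrees of freedom.

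| d | f² | λ = 468 × f² | Rejection rate at nominal 5% |
|---|---|---|---|
| 0 | 0 | 0 | 5.0% |
| 0.10 | 0.001875 | 0.878 | 10.6% |
| 0.15 | 0.004219 | 1.974 | 18.9% |

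**5. Sensitivity to the assumptions.** This uses the same layout, with an age SD of 13 years, healthy-group gaps of 3 to 10 years, correlations of 0.1 to 0.3 and N = 470. The rejection rate runs from 5.3% (3 years, ρ = 0.1) through 8.2% (5 years, ρ = 0.2) and 19.8% (10 years, ρ = 0.2) to 41.3% (10 years, ρ = 0.3). At the low end there is almost no inflation.

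**6. Does adjustment repair it?** Simulation, 4,000 runs, N = 468:

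| Age gap, ρ | ANOVA | ANCOVA with age |
|---|---|---|
| 5 years, 0.2 | 8.2% | 5.3% |
| 10 years, 0.2 | 19.6% | 4.8% |
| 10 years, 0.3 | 39.8% | 4.7% |
| 0 years, 0.3 | 4.8% | 4.8% |

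**7. Sex and chi-square.** Assume a yes/no feature present in 45% of men and 30% of women, 40% men in the healthy group and N = 470. The expected prevalence in the healthy group is 0.4 × 45% + 0.6 × 30% = 36%. With 50%, 60% or 70% men in the disease groups it is 37.5%, 39.0% or 40.5% there. The 3-df chi-square test rejects in 5.5%, 7.0% and 9.8% of cases.

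**8. Sample size gives no protection.** In a two-group t-test with the same spurious 0.10 and 0.15 SD, rejection is 11.8% and 20.6% with 116 v 116, and 19.0% and 36.5% with 232 v 233.

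**The case against.** The strongest reply is that section 2.7 is a short journal summary. It names test families by data type, does not call chi-square and ANOVA the sole basis for conclusions, and then adds logistic regression that may carry several independent variables. A covariate list is commonly left to the full protocol or the analysis plan, which are not shown. This stands in part: the absence of a list is not the finding, and the logistic sentence leaves room for adjustment. But a single tongue feature would satisfy that sentence, and it cannot adjust the chi-square and ANOVA comparisons. Those are stated methods, and for groups formed by diagnosis they are a weak choice.

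Second, for a screening tool, crude discrimination is a legitimate quantity. That is a good reason to keep the unadjusted results in the report. It does not cover the other stated aim, which is to describe how the tongue differs between diseases.

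Third, the exclusions in 2.2 remove several possible confounders. They do, but they do not balance age or sex.

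A reader might go further and infer that age and sex differences will be read as disease effects. The documents do not support that. Bias needs both an imbalance between groups and an effect of age or sex on the feature, and neither is reported.

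**Conclusion.** The point holds as a risk that the stated methods leave open, not as a demonstrated bias. The groups are not randomised, no matching is described, the named group comparisons are unadjusted, and the logistic regression commits to no covariates. Age or sex differences could therefore be mistaken for disease effects.

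Under the central assumptions (step 2 of the working) the false-positive rate of the planned four-group ANOVA is about 11% to 19% instead of 5%. The wider range tried runs from practically no inflation to about 41%, and the sex example is milder. All of these figures rest on assumed imbalances and associations. The change is worth making because the remedy is cheap and the unadjusted tests give no warning when the problem is present.

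**What to change.** In section 2.7:

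- Base the inferential group comparison of each tongue feature on a model with group, age (continuous) and sex. Use ANCOVA for continuous measures and logistic, ordinal or multinomial regression for categorical ones, with a rule set in advance for collapsing sparse levels.
- Include age and sex in every planned logistic model for disease.
- Report the unadjusted chi-square and ANOVA results alongside, so that crude discrimination remains visible.

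**Cost.** There is a modest amount of extra modelling, because section 2.5.1 lists many sub-measures under nine features, and some categories may be too sparse without merging. Age is already needed for eligibility and sex is routinely recorded, so no new data or patients are required. If the groups turn out balanced, little is lost: in the simulation with equal mean ages, both ANOVA and ANCOVA rejected in 4.8% of runs.

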**Objectives::**

The aim of this protocol is to apply a noninvasive ATDS to evaluate tongue manifestations of patients with upper gastrointestinal disorders and examine its efficacy as a diagnostic tool.

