#### Primary outcome measures

2.5.1

Nine primary tongue features will be extracted from the ATDS as follows: tongue shape: small and thin, moderate, large, and fat; tongue color: slightly white, slightly red, red, dark red, and dark purple; tooth mark: includes number, average covering area, maximum covering area, minimum covering area, and organs corresponding to the covering area; tongue fissure: amount, average covering area, shortest length, and longest length; fur color: white, yellow, and dye; fur thickness: none, thin, thick; fur amount, average covering area, maximum covering area, minimum covering area, and organs corresponding to the covering area; saliva: includes total area and the amount of saliva (none, little, normal, excessive); ecchymosis: amount, average covering area, maximum covering area, minimum covering area, and organs corresponding to the covering area; red dots: number, average covering area, maximum covering area, minimum covering area, and organs corresponding to the covering area.

Feature identification will be further subdivided into 5 segments (spleen–stomach, liver-gall-left, liver-gall-right, kidney, and heart–lung area) according to the theory of traditional Chinese medicine.

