#### Secondary outcome measures

2.5.2

Panendoscopy reports written by professional gastroenterology doctors will be recorded.

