## Discussion

3

According to the theory of traditional Chinese medicine, the tongue is thought to be an outer manifestation of the status of the viscera, and can be divided to spleen–stomach area, liver–gall area, kidney area, and heart–lung area. The tongue coating is formed by “stomach-Qi” and the 5 organs (“Wu-Zang” in Chinese) are also supplied by the stomach.^[19]^ Therefore, the tongue, especially spleen–stomach area, and the tongue coating may reflect the status of the spleen and stomach. The results of this trial are expected to provide valuable evidence supporting the use of tongue diagnosis to evaluate the status of patients with upper gastrointestinal disorders, helping clinical doctors to identify potential problems, and implement proper management of these conditions.

There are several studies that discuss the relationship between gastrointestinal disorders and tongue characteristics such as tongue coating thickness, tongue coating microbiota, and metabolic markers, and tongue temperature. Kim et al^[20]^ utilized the tongue coating thickness on patients with fuctional dyspepsia to assess the availability of tongue diagnosis system. Sun et al^[19]^ found that changes in metabolic pattern and miroecological index of tongue coating were associated with chronic gastritis. Cheng et al^[21]^ reported that patients suffering from gastrointestinal disease with *Helicobacter pylori* have a higher tongue temperature but have no statistically significance between the control group. However, the proposed study will provide more details and evidence of the usefulness of tongue image analysis for the identification of upper gastrointestinal disorders. In addition, this method of tongue diagnosis could be utilized in clinical practice and education.

There are 4 groups in this trial, namely, the peptic ulcer disease group, the gastroesophageal reflux group, the gastritis group, and the healthy group. Gastritis, PUD, and GERD are all associated with mucosa injury, but with different clinical manifestations and pathologies. We are interested in studying the differences between them, which might be visible on tongue images, and in assessing the relationship between panedoscopic images and tongue diagnosis.

In conclusion, TCM tongue diagnoses are expected to serve as preliminary screening indices for upper gastrointestinal disorders.

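### The study aims to test the tongue system as a diagnostic tool, but the planned analyses measure association and none measures accuracy against panendoscopy

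*Protocol article*

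**What the plan says.** The aim has two parts. The Objectives paragraph of the abstract wants to "evaluate tongue manifestations of patients with upper gastrointestinal disorders and examine its efficacy as a diagnostic tool". Section 2.3 (Study design) gives only the diagnostic part, and the Discussion ends with the expectation that "TCM tongue diagnoses are expected to serve as preliminary screening indices for upper gastrointestinal disorders".

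The design suits a diagnostic question. The tongue image is taken first and panendoscopy follows. Then: "According to findings of panendoscopy, the participants will be allocated to the following 4 groups" (peptic ulcer disease, reflux disease, gastritis, healthy).

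The outcomes are the tongue features (section 2.5.1: "Nine primary tongue features will be extracted from the ATDS as follows") and the endoscopy reports (section 2.5.2: "Panendoscopy reports written by professional gastroenterology doctors will be recorded"). Section 2.6 gives 517 participants from power 0.9, alpha 0.05, an effect size of 0.3 labelled r, and 10% drop-out.

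Section 2.7 states: "Chi-square tests will be applied for categorical data and Analysis of variance tests will be applied for continuous data". It adds: "Logistic regression will be used to estimate the odds ratio and the probability of a binary response, based on one or more independent variables". The criterion is P < .05. The binary response and the independent variables are not named.

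**The concern.** A diagnostic aim asks how well the tongue image separates people with disease from people without it, with panendoscopy as the arbiter. The usual answers are sensitivity, specificity and the area under the ROC curve (AUC). Chi-square tests, analysis of variance and odds ratios ask whether the groups differ on average. With several hundred participants, groups can differ significantly on a feature that classifies individuals little better than chance.

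At stake is the main conclusion. Followed as written, the study could find several significant tongue features and go on to claim diagnostic or screening value that it never measured.

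**Working it through.** **1. Aim against analysis**

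| Element | Where | What it concerns |
|---|---|---|
| Aim | Abstract, section 2.3 | Diagnostic efficacy, plus description of tongue manifestations |
| Expected use | Discussion | Preliminary screening |
| Outcomes | Sections 2.5.1, 2.5.2 | Tongue features; endoscopy reports recorded |
| Sample size | Section 2.6 | Generic effect size 0.3 |
| Analysis | Section 2.7 | Group differences, odds ratio, predicted probability |
| Criterion | Section 2.7 | P < .05 |

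Sensitivity, specificity, predictive values, AUC and a rule for a positive ATDS result appear nowhere in the article.

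**2. Reproducing 517**

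Inputs from section 2.6: effect 0.3, alpha 0.05, power 0.90, drop-out 10%. The test and sidedness are not stated, so several readings were tried. Where two totals are shown, the first is N × 1.1 and the second N / 0.9.

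- Two-sample t-test, d = 0.3, two-sided. The normal approximation is n per group = 2(1.960 + 1.282)² / 0.3² ≈ 234. The noncentral t gives 234.5, so 235 per group and 470 in total. 470 × 1.1 = **517**, an exact match (470 / 0.9 gives 523).
- Correlation r = 0.3, two-sided: 113, giving 125 or 126.
- Chi-square w = 0.3: 117 at 1 df, giving 129 or 130; 243 at 12 df, giving 268 or 270.
- Analysis of variance f = 0.3, four groups: 164, giving 181 or 183.
- Difference between two correlations, q = 0.3: 474, giving 522 or 527. This is close but not exact.

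The exact match is the two-group comparison of means. It remains an inference. None of these readings concerns accuracy.

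**3. What an effect of 0.3 means for classification**

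Assume a normally distributed feature with equal variance in both groups and a cut at the midpoint.

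- AUC = Φ(d/√2)
- Sensitivity = specificity = Φ(d/2)
- Odds ratio per SD = exp(d)

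Read as d = 0.3:

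- AUC = Φ(0.212) = 0.584
- Sensitivity = specificity = Φ(0.15) = 0.560
- Odds ratio = exp(0.3) = 1.35
- Power with 235 per group is 90%

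Read as r = 0.3 with balanced groups, d = 2 × 0.3 / √(1 − 0.09) = 0.629:

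- AUC = Φ(0.445) = 0.672
- Sensitivity = specificity = Φ(0.314) = 0.623
- Odds ratio = exp(0.629) = 1.88

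An AUC of 0.5 is chance.

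**4. Can the planned number support an accuracy analysis?**

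Evaluable participants: 517 × 0.9 ≈ 465. The article gives no share with disease, so take 25%, 50% and 75% as assumptions (116, 232 and 349 people). For a true sensitivity of 0.80, also assumed, the 95% half-width is 1.96√(0.80 × 0.20 / n):

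- n = 116: 0.073
- n = 232: 0.051
- n = 349: 0.042

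That precision is usable for any disease against healthy.

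**The case against.** The strongest reply is that a journal article condenses the plan. Cut-offs, model building, validation and predictive values are commonly left to the analysis plan, so their absence here is no finding. That is right, and the point does not rest on them. It rests on what the article does state: a diagnostic aim, alongside outcomes, a sample-size basis, tests and a success criterion that all concern association. An analysis plan that carried these out faithfully would still not measure accuracy.

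Two further replies stand. Chi-square and analysis of variance do serve the other stated aim, describing tongue manifestations and how they differ between groups. Panendoscopy already works as the reference standard in section 2.3, so its listing as a secondary outcome is a matter of labelling.

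A reader might infer more than the article supports:

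- *That the plan yields only group differences and odds ratios.* It also estimates a predicted probability, which could feed an ROC analysis. The article does not say that it will.
- *That performance will be judged on the patients used to fit the model.* The article plans no such assessment, in-sample or otherwise. Optimism is a reason to write the remedy carefully, not a stated defect.
- *That screening would have a poor predictive value.* If sensitivity and specificity were both 0.80, the positive predictive value would be 0.020 / (0.020 + 0.195) = 9% at the lowest East Asian reflux prevalence in the Introduction (2.5%), and 0.0624 / (0.0624 + 0.1844) = 25% at the highest (7.8%). At 50% it would be 80%, and the Introduction puts gastritis above half of the world's population. The figure depends on the target condition, so no general conclusion follows.

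**Conclusion.** The aim and the analysis do not match. Meeting P < .05 in section 2.7 is compatible with weak discrimination: AUC about 0.58 with sensitivity and specificity about 0.56 if 0.3 is a standardised mean difference, or about 0.67 and 0.62 if it is a correlation with balanced groups. The first reading is inferred from the exact match to 517. Both assume normality and equal variance, and describe a single feature; a model combining features could do better, but only an accuracy analysis would show it.

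This does not mean that the design is wrong or the study too small. The order of image and endoscopy is suitable, and about 465 evaluable participants would estimate a sensitivity of 0.80 to within 4 to 7 percentage points under the assumed disease shares. What needs correcting is the analysis tied to the diagnostic aim.

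**What to change.** 1. Name panendoscopy as the reference standard.
2. Keep chi-square and analysis of variance for the aim of describing tongue manifestations.
3. For the diagnostic aim, use the logistic regression already planned, with a defined binary response: any disease against healthy as the main contrast, each disease against healthy as further contrasts.
4. Pre-specify which measures from section 2.5.1 enter the model. That section names nine features but about 30 measures, before the division into five tongue segments, so the nine features alone do not settle the predictors.
5. Report AUC, sensitivity and specificity with 95% confidence intervals, at a cut-off fixed in advance or chosen within the resampling, corrected for optimism by bootstrap or cross-validation. The correction matters: in simulations with about 465 participants (25%, 50% or 75% diseased) and predictors carrying no information, the mean uncorrected AUC was about 0.58 to 0.59 with 9 predictors and 0.64 to 0.67 with 30.
6. Base any diagnostic or screening conclusion on these estimates, not on P-values or odds ratios.

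The cost is analysis wording and some extra programming on data already to be collected. The downside is that reported performance may look less favourable.

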### Sample size

2.6

We calculated the sample size will be 517 with power = 0.9, alpha = 0.05, effect size convention *r* = 0.3, and an anticipated drop-out rate of 10%, using G∗Power 3.0.1.0 software which is download from http://www.gpower.hhu.de.

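### Nine co-primary tongue features (30 listed measures) share one blanket P < .05 rule: a 37% chance of a false positive for nine independent tests, 79% for 30

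*Protocol article*

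**What the plan says.** Section 2.5.1 (Primary outcome measures) opens with "Nine primary tongue features will be extracted from the ATDS as follows". None of the nine is placed first, and each is described by between one and six measures. The same section adds: "Feature identification will be further subdivided into 5 segments".

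Section 2.3 forms four groups from the endoscopy findings: peptic ulcer disease, gastroesophageal reflux disease, gastritis and healthy. Section 2.7 (Data analysis) assigns chi-square tests to categorical data and analysis of variance to continuous data, and adds logistic regression. It closes with one criterion for all of them: P-"values <.05 will be considered statistically significance". It names no adjustment, order of testing or post-hoc procedure, and calls no test exploratory.

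Section 2.6 (Sample size) uses "power = 0.9, alpha = 0.05", "effect size convention *r* = 0.3" and 10% dropout to reach 517. The Discussion says of the three diseases: "We are interested in studying the differences between them, which might be visible on tongue images".

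**The concern.** A threshold of .05 applied separately to each of many primary tests does not hold the overall false positive rate at 5%. With nine co-primary features the rate is already several times nominal, and it grows if each listed measure is tested. The sample size section shows the same habit: one alpha of 0.05, as if there were one test.

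The study aims to examine the system as a diagnostic tool, and the Discussion expects evidence in support of tongue diagnosis as a preliminary screening index. Under the stated rule, a reader of the results could not tell a real tongue marker from the false hits that the rule itself is expected to produce.

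**Working it through.** **The plan's own figure.** Inputs from section 2.6: power 0.9, alpha 0.05, effect 0.3, dropout 10%. A two-sided, two-group t-test with d = 0.3 and equal groups needs 235 per group, 470 in all, and 470 × 1.10 = 517. Of the designs tried, this is the only one that returns 517 exactly. Before dropout, the others give:

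- correlation r = 0.3: 113
- chi-square with w = 0.3 and 1 to 15 degrees of freedom: 117 to 263
- four-group analysis of variance with f = 0.3: 162
- one-sided t-test with d = 0.3: 382

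So 517 rests on one comparison at an undivided 0.05.

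**Count of measures (section 2.5.1).** Shape 1, tongue colour 1, tooth mark 5, fissure 4, fur colour 1, fur thickness 1 plus 5 fur measures, saliva 2, ecchymosis 5, red dots 5. Total: 1 + 1 + 5 + 4 + 1 + 6 + 2 + 5 + 5 = 30.

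**Upper bound with segments.** 30 × 5 = 150. Shape describes the whole tongue, and the four items on corresponding organs appear to record location already. Leaving out these five gives 25 × 5 = 125.

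**False positives.** Assume no true association and m independent tests at 0.05. The chance of at least one is 1 − 0.95^m, and the expected number is 0.05 × m.

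| Tests m | Chance of at least one | Expected number |
|---|---|---|
| 9 features | 1 − 0.630 = 0.370 | 0.45 |
| 30 measures | 1 − 0.215 = 0.785 | 1.5 |
| 125 (segments, reduced) | 0.998 | 6.25 |
| 150 (segments, full) | 0.9995 | 7.5 |

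**Correlation.** The documents give no correlations, so a range was simulated for four-group overall tests. As the assumed within-feature correlation rises from 0.3 to 0.9, the chance of at least one false positive falls from about 0.77 to 0.49 for 30 tests, and from about 0.997 to 0.70 for 150. At 0.7 the figure for 150 is still 0.91. The expected counts stay at about 1.5 and 7.5 throughout.

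**Power at the strictest Holm step.** This step uses 0.05/9 = 0.0056.

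- *If 0.3 is Cohen's w.* N = 517 × 0.90 = 465, noncentrality 465 × 0.3² = 41.85. Power is 0.999 (3 degrees of freedom), 0.996 (6), 0.991 (9) and 0.983 (12).
- *If 0.3 is d in two groups of 235.* Noncentrality is 0.3 × √(235/2) = 3.25. Power is 0.90 at 0.05 and about 0.68 at 0.0056.

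Holm's later steps use larger thresholds, so no single feature has lower power than at this step.

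**The case against.** The strongest reply is that the lack of adjustment is inferred from silence. Section 2.7 does not say that the P-values are unadjusted, and adjusted P-values are also compared with .05. Multiplicity procedures are often left to an analysis plan, which is not shown, and this is a condensed article. That limits the point: a missing adjustment alone would be no finding. What remains is what the article fixes: nine unranked primary features, one .05 criterion for every test, and a sample size at undivided alpha.

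Four stronger readings are tempting and not supported:

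- *False positives are close to certain.* That needs 125 to 150 segment-level tests. Section 2.5.1 subdivides feature identification, but section 2.7 does not explicitly plan tests by segment, and high correlation would lower the figure.
- *Four groups multiply the tests.* Chi-square and analysis of variance give one overall test per measure. The six pairwise contrasts per measure would have to be inferred from a sentence of interest in the Discussion.
- *One significant feature would be taken as proof.* Section 2.7 defines significance only; nowhere is one hit said to suffice for concluding that the tongue reflects disease.
- *Adjustment costs almost nothing.* That holds only if 0.3 is Cohen's w. The article labels it r, and 517 is reproduced with d.

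It can also be said that an observational study of this kind needs no adjustment. If it were declared exploratory, that would answer the concern. The article instead names primary outcomes, gives a power calculation and states a diagnostic aim.

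**Conclusion.** The concern holds in this limited form and should be fixed. Followed as written, the .05 rule gives about 37% family-wise error for one test per primary feature, more than seven times nominal, and about 79% if all 30 measures are tested. Both figures assume no true association and independent tests; correlation reduces them but leaves 0.45 and 1.5 false positives expected. The figure above 99% is an upper bound, conditional on segment-level testing that the analysis section does not state.

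The remedy is mainly a change of wording, but its effect on power depends on what the effect size of 0.3 means, which the article leaves unclear.

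**What to change.** Replace the blanket .05 sentence in section 2.7 with a rule along these lines:

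1. Name one measure per feature as primary, and test the nine four-group comparisons with Holm at a family-wise 0.05.
2. Run the pairwise contrasts for a feature only after its overall test is significant under step 1, with Holm adjustment.
3. Label the remaining measures and all segment-level tests exploratory, with Benjamini-Hochberg control of the false discovery rate.

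The choice of measures should be fixed before the groups are compared.

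The cost is lower power per test. Section 2.6 should say what kind of effect the 0.3 is and restate the power of 0.9 for the adjusted primary tests. On the two readings above, power at the strictest step is 0.98 to 0.999 (Cohen's w) or about 0.68 (two-group d). This fix does not require a larger sample, but if the two-group reading is the intended one, the lower power should be stated openly.
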